**Objective:**

To determine whether adding an online peer influencer led WhatsApp intervention to standard FM radio and WhatsApp HIV messaging increases HIV testing uptake among young adult men aged 18–32 years in Nairobi, Kenya.

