Although WhatsApp based interventions and peer led approaches have independently demonstrated effectiveness in improving HIV related outcomes, evidence evaluating the additional benefit of adding online peer influencer engagement to standard radio and social media based, HIV testing interventions for young men remains limited. This study addresses that important evidence gap by determining whether adding an online peer influencer component to standard FM radio and WhatsApp, HIV messaging, results in greater HIV testing uptake among young adult men in Nairobi.

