### Sample size determination

2.8

The primary outcome of this trial is HIV testing uptake, defined as completion of at least one HIV test during the study period. Because the primary outcome is binary and reported as a population proportion, the sample size was estimated using Cochran’s formula for proportions (22).

$$n0=(Z^{2}\cdot p\cdot q)/e^{2}$$

Where *Z* represents the critical value for a 95% confidence level (1.96), *e* denotes the acceptable margin of error (0.05), and p represents the estimated baseline proportion of HIV testing uptake. Given that the true HIV testing prevalence within this online male demographic was undetermined, *p* was conservatively set at 0.50 (*q* = 1 − *p* = 0.50) to assume maximum population variance and yield the most conservative sample size baseline. This primary calculation established a baseline requirement of 384 participants. To account for anticipated digital non-response and loss to follow-up, an approximate 22% attrition adjustment was applied (inflating the sample via *n* = *n*₀/0.82), resulting in a final cleared sample size of 468 participants allocated equally across the three study arms in a 1:1:1 ratio (156 participants per arm). Within each arm, participants will be stratified by age group prior to simple randomization to preserve developmental balance.

To validate this allocation against the primary objective, a supplementary power assessment was conducted using the standard formula for comparing two independent proportions:

$$n=[{\left(Z\_\{\alpha /2\}+Z\_\beta \right)}^{2}\cdot (p₁(1-p₁)+p₂(1-p₂))]/{\left(p₁-p₂\right)}^{2}$$

Where *α* is fixed at a two-sided significance level of 0.05 (*Z*_{*α*/2} = 1.96) and statistical power is fixed at 80% (*Z*_*β* = 0.84). Based on evidence highlighting depressed health seeking behaviors among young men in Kenya alongside historical peer led intervention data demonstrating up to 50% relative increases in testing uptake within sub-Saharan Africa, the calculation assumed an expected HIV testing uptake rate of 20% (*p*₁) in the active control arm and 40% (*p*₂) in the intervention arms (15, 16). This establishes an estimated absolute effect size of 20 percentage points.

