Processing these assumptions confirms that an allocation of 156 participants per arm is statistically sufficient to detect absolute differences of approximately 20 percentage points between any single intervention arm and the active control group. While generalized linear mixed models (GLMMs) will be implemented for the longitudinal analysis of repeated outcome measurements, these serve purely as analytical frameworks rather than sample size estimation methods (17, 23). The trial is explicitly not powered to identify subtle variations within participant subgroups or to support definitive head-to-head hypothesis testing between the two intervention arms.

The study is powered to detect large intervention effects of approximately 20 percentage points in HIV testing uptake between study arms at a two-sided significance level of 0.05 and 80% statistical power. Subgroup analyses will be considered exploratory and interpreted cautiously (42).

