### Intervention Arms

2.10

Participants will be randomly allocated to one of three intervention arms of increasing intervention intensity.

*Arm 1 (active control)*: participants will receive routine HIV promotion messages broadcast through the partner FM radio station.

*Arm 2 (standard digital messaging)*: participants will receive the FM radio intervention together with standardized HIV related WhatsApp messages delivered through closed WhatsApp study group.

*Arm 3 (peer influencer intervention)*: participants will receive the FM radio intervention, standardized WhatsApp messaging, and additional engagement from trained online peer influencers who will facilitate discussions, share structured HIV testing messages, provide behavioral prompts and reminders, answer general questions, and encourage HIV testing at the partner HIV Testing Services (HTS) facility.

Interventions will be delivered over a 12-week period.

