### Statistical analysis

2.19

All analyses will follow a prespecified Statistical Analysis Plan (SAP) deposited with the PACTR registry. Analyses will be conducted under an intention-to-treat framework to preserve randomization integrity (36).

A two sided significance level of 0.05 will be used throughout, with 95% confidence intervals reported (48).

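### The power check said to validate the primary objective covers comparisons with Arm 1 only, while the objective is Arm 3 versus Arm 2, a contrast the plan disclaims

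*Protocol article*

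**What the plan says.** **The question.** The abstract's Objective is to find out whether "adding an online peer influencer led WhatsApp intervention to standard FM radio and WhatsApp HIV messaging increases HIV testing uptake". The Introduction gives the evidence gap in the same terms: "determining whether adding an online peer influencer component to standard FM radio and WhatsApp, HIV messaging, results in greater HIV testing uptake". The Discussion (section 3) repeats it.

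**The arms (section 2.10).** Arm 1 is FM radio messaging. In Arm 2, "participants will receive the FM radio intervention together with standardized HIV related WhatsApp messages". Arm 3 is the Arm 2 content plus engagement by trained peer influencers.

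**The sample size (section 2.8).** The 468 comes from Cochran's formula for estimating one proportion. A supplementary two-proportion calculation is then offered as validation against the primary objective. It takes uptake of 20% "in the active control arm and 40"% in the intervention arms, and concludes that 156 per arm is enough for either intervention arm against the active control. The same paragraph ends by saying that the trial is not powered for subgroup differences "or to support definitive head-to-head hypothesis testing between the two intervention arms". The next paragraph says: "The study is powered to detect large intervention effects of approximately 20 percentage points in HIV testing uptake between study arms". It does not say which arms.

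**The analysis (section 2.19).** "A two sided significance level of 0.05 will be used throughout". The primary model has arm, time and their interaction. The article does not single out a pair of arms.

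**The concern.** Only Arm 3 versus Arm 2 isolates the influencers, because those two arms otherwise receive the same radio and WhatsApp content. Arm 3 versus Arm 1 mixes the effect of WhatsApp messaging with the effect of influencers. It could be large and significant even if influencers added nothing.

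The plan shows power for the mixed comparison, presents this as validation of the objective, and disclaims the comparison the objective needs. It then makes a power statement broad enough to cover every pair. A reader cannot tell whether an Arm 3 versus Arm 2 result is meant to be conclusive. What is at stake is the headline claim: a significant Arm 3 versus Arm 1 result could be reported as evidence that influencers add value, and a non-significant Arm 3 versus Arm 2 result could be read as evidence that they do not.

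**Working it through.** **1. The plan's own figures (inputs from section 2.8).**
- Cochran: 1.96² × 0.50 × 0.50 / 0.05² = 384.2. Dividing 384 by 0.82 gives 468.3, so 468, or 156 per arm. This reproduces. No between-arm difference enters the formula.
- Supplementary check, by the plan's formula: (1.96 + 0.84)² × (0.20 × 0.80 + 0.40 × 0.60) / 0.20² = 7.84 × 0.40 / 0.04 = 78.4, so 79 per arm. The statement that 156 suffices reproduces for an intervention arm against Arm 1.

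**2. Power for the Arm 1 comparison.** Normal approximation, two-sided 0.05, n per arm, d = p₂ − p₁, p̄ the mean of the two rates:

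power = Φ{ [d√n − 1.96√(2p̄(1 − p̄))] / √(p₁(1 − p₁) + p₂(1 − p₂)) }

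- 20% versus 40%, n = 156: (2.498 − 1.270) / 0.632 = 1.94, power 97%.
- n = 128 (384/3, the evaluable number after the plan's attrition allowance): (2.263 − 1.270) / 0.632 = 1.57, power 94%.

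**3. The contrast in the objective.** The plan states no Arm 3 versus Arm 2 difference. It uses 40% for whichever intervention arm is compared with control. I therefore assume 40% in Arm 2 and show a range for Arm 3. Participants are treated as independent.

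| Arm 2 → Arm 3 | Increment | Power, 156 per arm | Power, 128 per arm |
|---|---|---|---|
| 40% → 45% | 5 points | 14% | 12% |
| 40% → 50% | 10 points | 43% | 36% |
| 40% → 55% | 15 points | 76% | 67% |
| 40% → 60% | 20 points | 95% | 90% |

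Worked line for 10 points, n = 156: (1.249 − 1.379) / 0.700 = −0.186, and Φ(−0.186) = 0.43. For n = 128: (1.131 − 1.379) / 0.700 = −0.354, and Φ(−0.354) = 0.36.

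The smallest increment with 80% power from 40% is 15.8 points (156 per arm) or 17.4 points (128 per arm). From an assumed 30% in Arm 2 it is 15.3 or 17.0 points.

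**4. Size needed for a smaller increment.** For 80% power at 40% versus 50%, 388 evaluable per arm are needed. With the plan's allowance, 388/0.82 gives 474 per arm, or 1,422 over three arms.

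**5. Setting the statements of section 2.8 side by side.** The claim of validation against the primary objective is not met, because the check never involves Arm 3 versus Arm 2. The disclaimer withholds a definitive test of that pair. The closing power statement does not exclude it. All three cannot stand beside the stated objective.

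**The case against.** **The strongest defence is that the disclaimer is honest.** If influencers add 5 or 10 points to an already active WhatsApp arm, the trial is underpowered for that, and saying so is right. This stands in part: the caveat has real content and should not simply be struck out. But it concerns the one question the protocol says it asks, and it gives no figure that tells a reader which increments are within reach.

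**The SAP may name the primary contrast and deal with multiplicity.** This stands. The SAP is not shown, so their absence from the article is not part of this point. A named contrast in the SAP would not, however, correct the article's claim that the Arm 1 check validates the objective.

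**Stronger readings a reader might infer, which the document does not support:**
- *The trial cannot answer its question at all.* Arm 3 versus Arm 2 is randomized and can be estimated, and power is 90% to 95% for 40% versus 60%. For that pair the closing 20-point statement is arithmetically true under the assumed 40%.
- *The plan expects no influencer effect, since both intervention arms are set at 40%.* The 40% is a planning value for either arm against control, not a forecast that the two are equal.
- *Three unadjusted pairwise tests are planned, with success on any of them.* The document sets 0.05 throughout and specifies one mixed model. It neither lists three pairwise tests nor defines success that way.
- *The trial was sized on the Arm 1 comparison.* The 468 comes from the one-proportion formula; the Arm 1 comparison is a supplementary check.

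**Conclusion.** The point holds as an inconsistency that must be resolved. The power check does not validate the stated primary objective, and the two closing paragraphs of section 2.8 leave the status of Arm 3 versus Arm 2 unclear. A significant Arm 3 versus Arm 1 result would not show that influencers add anything.

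For the objective's own contrast, the current size gives 80% power for about 16 points (156 per arm) or 17 points (128 evaluable). A null result would therefore not exclude smaller benefits: at 10 points, power is only about 43% or 36%.

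These figures rest on an assumed 40% in Arm 2, the normal approximation, and independent participants. The last assumption is favourable, since Arms 2 and 3 are delivered in closed WhatsApp groups. As an illustration only, assume groups of 52 and an intraclass correlation of 0.01 to 0.02 in both arms. The design effect is 1 + 51 × 0.01 = 1.51 to 1 + 51 × 0.02 = 2.02, and multiplying by its square root raises the detectable difference to about 19–22 points (156) or 21–25 points (128).

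**What to change.** **Preferred.** In section 2.8, state that Arm 3 versus Arm 2 is the contrast that answers the objective. Replace both the blanket head-to-head disclaimer and the unqualified sentence about power between study arms with the detectable difference for that contrast: 80% power for about 16 points from an assumed 40% in Arm 2 with 156 per arm, or about 17 points with 128 evaluable, assuming independent participants. Add that power for a 10-point increment is about 43% (36%), so a null result would not exclude smaller benefits. Describe the 20% versus 40% check as applying to comparisons with Arm 1, and drop the statement that it validates the primary objective.

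**Alternative.** If the sponsor wants the comparison with Arm 1 to carry the conclusion, reword the objective and the conclusion to that comparison and call Arm 3 versus Arm 2 exploratory.

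**Cost.** Either route is a change of wording at the current 468, to be carried into the SAP. The price of the first is a less favourable power statement; the price of the second is a narrower claim than the evidence gap the protocol sets out to fill. Any order of testing among the three comparisons is a separate trade-off for the sponsor, and this point does not require one.

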### Stratification, randomization and allocation

2.9

Following consent and baseline assessment, participants will be stratified into three prespecified age groups:

*Stratum A*: 18–22 years (Young Gen Z)*Stratum B*: 23–27 years (Older Gen Z)*Stratum C*: 28–32 years (Young Millennials)

This stratification approach is informed by evidence demonstrating age related differences in HIV testing uptake and health seeking behaviors among young men (24), as well as variation in peer influence within social networks (25).

Each stratum will include 156 participants, with equal allocation across study arms (52 participants per arm per stratum), yielding a total sample size of 468 participants.

Within each stratum, participants will be randomly assigned in a 1:1:1 ratio using computer generated block randomization with a fixed block size of six. Randomization sequences will be prepared independently before recruitment by an independent randomization officer not involved in enrolment.

Allocation concealment will be maintained using centralized password-protected computerized randomization. Recruitment staff will remain unaware of future allocations until assignment has occurred (see Figures 1, 2).

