### Online peer influencer intervention

2.11

A total of 15 online peer influencers (five per age stratum) will be identified using social network analysis (SNA) methods. This approach enables objective selection of individuals with high influence within digital networks, improving intervention reach and effectiveness compared to convenience-based peer educator models (25).

Peer influencers will complete standardized virtual training covering HIV communication, ethical conduct, participant engagement, confidentiality, and referral procedures. Throughout the intervention they will receive ongoing supervision, weekly monitoring, and fidelity assessments.

Peer influencers will facilitate WhatsApp discussions, encourage HIV testing, distribute referral information, and support participant engagement. They will not participate in recruitment, randomization, outcome assessment, or data analysis (44).

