### Masking

2.13

Because of the behavioral nature of the intervention, participants and peer influencers cannot be blinded.

Outcome verification will be conducted independently wherever feasible, while data analysts will analyze masked treatment codes until completion of the primary analyses.

This partial masking approach is consistent with best practices for non pharmacologic trials and is intended to reduce ascertainment and analytical bias (27) (see Figure 3).

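### A fixed, published block size of six does not guarantee the promised concealment: staff who can see past assignments by age stratum could deduce up to one in five allocations

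*Protocol article*

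**What the plan says.** Section 2.9 sets the scheme: "Within each stratum, participants will be randomly assigned in a 1:1:1 ratio" by "computer generated block randomization with a fixed block size of six". The target is stated as "Each stratum will include 156 participants, with equal allocation across study arms (52 participants per arm per stratum), yielding a total sample size of 468". The sequences are to be "prepared independently before recruitment by an independent randomization officer not involved in enrolment", and "Allocation concealment will be maintained using centralized password-protected computerized randomization". The section ends with an unqualified promise: "Recruitment staff will remain unaware of future allocations until assignment has occurred".

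Section 2.13 (Masking) says that "participants and peer influencers cannot be blinded" and that analysts work on masked codes. It does not mention whether recruitment staff know the arms of men already randomized. Section 2.11 says of the peer influencers: "They will not participate in recruitment, randomization, outcome assessment, or data analysis".

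Sections 2.4.4 and 2.6 run the whole path from screening to follow-up online, and 2.9 places randomization after consent and the baseline assessment. Section 2.8, in its sample size text, refers instead to simple randomization after age stratification.

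**The concern.** A locked central list stops staff from reading the sequence. It does not stop them from inferring it. With a known, constant block size, a count of the assignments made so far in a stratum shows where the current block stands and which arms still have places. There is no stratification by site, so each stratum is one run of consecutive blocks starting at its first man, and the block boundaries are easy to count. The wording of the promise, which runs only up to the moment of assignment, leaves open that staff learn each arm afterwards.

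The primary outcome is attending for an HIV test, which depends heavily on personal motivation. If whoever handles queries, reminders or the timing of enrolment could foresee the next arm, keener men could be drawn towards one arm, knowingly or not. Intention-to-treat analysis and analyst masking would not repair such an imbalance. Because participants cannot be blinded, concealment of the next allocation is a main safeguard against selection bias.

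**Working it through.** **Inputs** (all from 2.9): block size 6, fixed; three arms at 1:1:1, so 2 + 2 + 2 places per block; 156 men per stratum; three strata.

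**The plan's own figures.** 3 × 156 = 468; 156 / 3 = 52 per arm per stratum; 156 / 6 = 26 complete blocks per stratum, 78 in all. These agree with each other. The article gives no figure for predictability.

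**Observer assumed.** Someone who knows the block size and sees every earlier assignment in that stratum, in order.

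**Orderings of one block.** 6! / (2! × 2! × 2!) = 90.

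| Slot | Known with certainty | At least one arm ruled out | Best guess correct |
|---|---|---|---|
| 1 | 0 | 0 | 1/3 = 0.333 |
| 2 | 0 | 0 | 2/5 = 0.400 |
| 3 | 0 | 18/90 = 0.2 | 2/4 = 0.500 |
| 4 | 0 | 0.6 | 0.4 × 1/3 + 0.6 × 2/3 = 0.533 |
| 5 | 18/90 = 0.2 | 1 | 0.2 × 1 + 0.8 × 1/2 = 0.600 |
| 6 | 90/90 = 1 | 1 | 1 |
| Sum | 1.2 | 2.8 | 3.367 |

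Slot 5 is certain when the last two places belong to the same arm: 3 arms × 6 orderings of the other four places = 18. Slot 4 is never certain, because three places remain and no arm has more than two.

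- Known with certainty: 1.2 / 6 = 20.0%; 26 × 1.2 = 31.2 per stratum; 78 × 1.2 = 93.6 of 468.
- At least one arm ruled out: 2.8 / 6 = 46.7%; 78 × 2.8 = 218.4 of 468.
- Best guess correct: 3.367 / 6 = 56.1%, against 33.3% by chance.

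**Effect of varying the size.** Simulation of 300 strata of 156 men, with block sizes drawn at random in equal shares. The observer knows the set of sizes but not the size of each block. The simulation did not force the last block to end exactly at 156.

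| Block sizes | Known with certainty | Best guess correct |
|---|---|---|
| 6 fixed (check on the exact result) | 19.9% | 56.2% |
| 3, 6 or 9 | 3.8% | 55.3% |
| 6 or 9 | 5.1% | 54.1% |
| 6, 9 or 12 | 2.5% | 52.8% |

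With 3, 6 or 9, certain predictions drop to 0.038 × 468, or about 18 men. A larger fixed block does much less: by exact calculation, a fixed size of 9 still leaves 14.3% certain and a fixed size of 12 leaves 11.1%.

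All of this applies only to the block scheme of 2.9. Under the simple randomization named in 2.8 past assignments would reveal nothing, but 52 per arm per stratum could not be guaranteed either.

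**The case against.** The strongest reply is that the key step is not in the article. Nothing says that recruitment staff see assigned arms cumulatively, by stratum and in order. The sequence is held centrally and prepared by someone outside enrolment. Who places men in their WhatsApp groups is not described, and the workflow diagram (Figure 2), which might settle it, is not available here. Nor does the article say whether men are randomized one at a time or in batches. This stands: the 20% is conditional.

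A reader might infer that concealment fails outright, or that anyone who sees an assignment can predict the next. The documents do not support either. A participant or influencer sees one arm's closed group, not the ordered list across arms, and 2.11 keeps influencers out of recruitment and randomization. That they are unblinded does not by itself open the sequence.

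The opportunity to act on a guess is also limited. Eligibility rests on simple facts, screening and consent are electronic, and randomization follows consent and baseline. This narrows the scope for steering but does not remove it, because the timing of reminders, replies to queries and release for randomization is not described as automatic.

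Finally, the 56% best-guess rate should not be charged to the fixed size. It comes mostly from small balanced blocks, and varying their size hardly changes it. That is correct, and it is why varying blocks alone are not a full remedy.

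What the reply does not answer is that the article itself states the block size, calls it fixed and publishes it, beside an unqualified promise that this scheme cannot secure alone.

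**Conclusion.** The point holds in conditional form. As written, 2.9 does not guarantee that recruitment staff stay unaware of future allocations. Up to 20% of allocations (about 94 of 468) could be deduced with certainty.

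This rests on three assumptions: blocks of six are used as in 2.9 and not simple randomization as in 2.8; men are assigned one by one; and someone involved in enrolment can see earlier assignments in order within a stratum. If any of these fails, the certain share is lower or zero. The documents show neither that concealment has been lost nor that selection bias will follow, and they give no basis for estimating the size of such a bias. The change is still worth making, because it is nearly free and the trial is open, with an outcome that depends on motivation.

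**What to change.** 1. In 2.9, replace the fixed block size with randomly varying permuted blocks within each age stratum, for example 3, 6 and 9. Constrain the total to 156 per stratum; since 156 is a multiple of 3, the last block can always be chosen to fit and 52 per arm is kept.
2. Keep the sizes in a restricted document held by the independent randomization officer, and do not disclose them to recruitment staff.
3. Because guessing better than chance remains possible, also state that enrolling staff cannot see assigned arms by stratum. Alternatively, randomize each stratum in one batch once all its men have consented and completed baseline; that removes the problem.
4. Reconcile the simple randomization in 2.8 with the block randomization in 2.9, so that one method is described throughout.

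The cost is a regenerated list, slightly more complex list generation and a few sentences of text. The batch option would also make early recruits wait until their stratum is full. The article describes recruitment in the future tense, so the change can be made before the list is used.
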